## Abstract

**Background:**

Of the 150 000 people per year in the UK who have strokes, third to half will experience a so-called ‘minor stroke’. Although appearing benign these strokes put a person at increased risk of further strokes and survivors are usually considered ‘too good’ for referral onto community stroke services. When back at home the hidden effects of stroke like fatigue and changes in mood and cognition become apparent and impact return to work, relationships and everyday activities. Alongside this, managing the risk of recurrence, highest early after an initial stroke, is a priority. People with stroke report feeling abandoned after discharge with unmet information and support needs.

**Methods:**

To address this issue, we reviewed the literature, met with people with stroke and other stakeholders to develop an early, personalised follow-up programme of care for those who currently only receive routine medical follow-up appointments. The design of this complex intervention is informed by the NIHR/MRC framework for complex intervention development and the framework of action described by O’Cathain and colleagues. The intervention is underpinned by self-determination theory. We will be conducting a randomised, mixed methods, single-centre feasibility study to explore the acceptability and feasibility of the intervention. Sixty participants will be recruited from a Hyperacute Stroke Unit and Rapid Assessment Clinic and randomised to the intervention or control group. The intervention group will receive personalised follow-up appointments at two- and six-weeks post-discharge. All participants will have outcome measures taken at baseline and twelve-weeks post-stroke. Patient reported outcomes will be reviewed to assess their suitability for a later definitive trial. Qualitative interviews will be conducted to gain a deeper understanding of life after stroke from those who did and did not receive the intervention.

**Conclusions:**

Study findings will be used to further refine the intervention, methods and outcome measurements used. These refinements will inform a future multicentre randomised controlled trial.

## Introduction

### Background and rationale

**
*The size of the problem*
**

Stroke is the leading cause of disability in the UK and there are 1.3 million people living with the after-effects of stroke
^
1
^. Of the 150 000 strokes occurring per year, a third to a half of these are minor strokes
^
2,
3
^. The incidence and prevalence of stroke are increasing
^
4
^ and the economic burden of stroke on society, health, social care, and the person and their family is significant
^
5
^. A large population-based study in the United Kingdom showed a decline in stroke mortality rates
^
6
^. However, there has been an increase in the event rates in the 35–54 age group
^
6
^. The total annual societal cost of stroke in the UK is £26 billion; the largest portion of these costs, £20.6 billion, relates to the provision of ongoing care
^
5
^. 

**
*The importance of the problem*
**

Large-scale policy initiatives, such as the NHS Long Term Plan
^
7
^ and the Stroke Plan for Europe
^
8
^ have recognised the importance of improving stroke services. They are calling for a focus on improving life after stroke by improving how services work together and empowering people with stroke to manage their risk of further stroke and optimise their quality of life. Stroke shares many risk factors with cardiovascular disease (CVD), one of the largest contributors to health inequality
^
9
^. One-fifth of the life expectancy gap between the most- and least-deprived communities is attributable to cardiovascular disease. Stroke is more common in people from South Asian and Black communities and they have the highest risk of CVD
^
9
^. Stroke and cardiovascular disease can often be prevented by leading a healthy lifestyle; however, this requires communities that are supported, informed, and engaged. We also know that evidence-based treatments to reduce recurrence of stroke exist and yet evidence from a large South London Stroke Registry study has shown that the incidence of secondary stroke has not reduced since 2005
^
10
^. These data indicate that the implementation of secondary prevention programmes has not yet been optimised.

The James Lind Alliance research priority setting partnership ensures that the voices of people with stroke carry equal weight to those of clinicians and researchers. Their stroke priority setting partnership report identified priority research areas that align with this research
^
11
^:

-What can stroke survivors do to reduce the risk of having another stroke?-What are the best interventions to promote recovery and prevent further stroke in people who have had strokes?-How can we recognise, assess, treat, and support people who experience hidden impairments (psychological problems, cognitive and communication changes, and fatigue) after a stroke?

**
*What is a minor stroke?*
**

There is no universally agreed definition for minor stroke
^
12,
13
^ and the terminology used, such as minor, mild, mini, and non-disabling, is confusing. In this feasibility study, we will use the tissue-based definition
^
14
^ for minor stroke (a stroke visible on imaging).
*
The definition we use for TIA is the presence of transient neurological symptoms which appear to have fully resolved within 24 hours and the absence of tissue damage on brain imaging. The National Institute for Health Stroke Scale (NIHSS) score is an impairment scale which is widely used in clinical practice and research to define minor, moderate or severe stroke (see
Table 1)
^
15
^.
The most commonly used cut off points for minor stroke in research studies are NIHSS ≤ 3 or NIHSS ≤ 5
^
16
^.
We will be using NIHSS ≤ 5 as our cut off point in this study.*

**Table 1. T1:** Modified Rankin scale.

Level	Description
0	No Symptoms
1	No significant disability, despite symptoms; able to perform all usual duties and activities
2	Slight disability: unable to perform all previous activities but able to look after own affairs without assistance.
3	Moderate disability: requires some help, but able to walk without assistance.
4	Moderate severe disability: unable to attend to own bodily needs without assistance and unable to walk unassisted.
5	Severe disability: requires constant nursing care and attention, bedridden, incontinent.

*
In our service the medical management of those with both minor stroke and TIA focuses on the identification and management of vascular risk factors. Both people with a diagnosis of TIA or minor stroke will have a therapy assessment on the HASU. Only those with a minor stroke are referred for a six-month stroke review. Community stroke therapy teams that subscribe to the time-based definition for TIA will usually not accept referrals for people with a diagnosis of TIA
*.

Hyperacute treatments such as thrombolysis and thrombectomy improve survival post-stroke, and increasing numbers of people are discharged home with minimal physical disability. This scenario requires further attention from healthcare services and society. People with stroke say that a life saved is a life worth living, and services need to improve and change the focus from surviving to thriving
^
17
^.

**
*What is a complex intervention?*
**

Many interventions used in healthcare are considered to be complex interventions, whereby the intervention consists of a number of different interacting components, each targeting different areas of behavioral change or aspects of health and wellbeing. Complex interventions allow a degree of flexibility as they are applied in different contexts or different systems to a wide range of individuals with varying levels of health literacy and from a diverse range of communities
^
18
^.

**
*What happens in current practice?*
**

People with minor stroke typically have a very short length of stay in hospital or are increasingly being managed in outpatient clinics and emergency departments
^
19
^. The clinical team focuses on ruling out obvious physical, cognitive, and communication difficulties. The assessment tools used are generally insufficiently sensitive to pick-up high-level impairments
^
20,
21
^. People consistently report that they receive insufficient personalised information prior to discharge
^
22
^. The discharge summary is written with the general practitioner in mind and is often difficult for laypeople to understand. On discharge home, the person with stroke describes feeling abandoned and lost
^
22,
23
^. Given the lack of information provision and the inaccessible nature of discharge summaries to lay persons, it is not surprising that up to a third of people with stroke and TIA will have discontinued their medication within a year of discharge
^
24
^.

Current medical follow-up appointments are brief and focus specifically on medical issues and outstanding medical investigations. Ideally, these should occur 6 weeks post-discharge, but in practice, the wait for these appointments is often longer. These appointments rarely have multidisciplinary input; therefore, other issues relating to hidden effects, adjustment to life after stroke, and secondary prevention are seldom addressed. National Clinical Guidelines for Stroke (2023) recommend that all people after stroke should receive a holistic and structured 6-month review
^
25
^.

We conducted a scoping review to identify follow-up programmes, pathways, and services that have been developed for people after minor stroke
^
26
^. Twenty-five studies were included in the analysis. Interventions often focused on education, secondary prevention, and exercise after stroke, whereas the management of hidden impairments and adjustment to life after stroke were less likely to be addressed. These complex interventions were often poorly described, and descriptions of family involvement, liaison between primary and secondary care, and underpinning psychological or behavioural theories were lacking. The review revealed that it is still unknown how best to organise services to offer personalised timely support and education to people in the community. There were two RCTs included in the scoping review, (STROKE-CARD
^
27
^ and ‘Take Charge’
^
28
^) that were able to demonstrate improvements in health-related quality of life at 12 months after the stroke. STROKE-CARD involved personalised, comprehensive multidisciplinary follow-up at 3 months post stroke and the Take Charge follow-up intervention was underpinned by self-determination theory and involved either one or two follow-up appointments. Take Charge’s person centred intervention focused on supporting a person to take charge of their recovery through supporting self-empowerment. The key elements from these two studies; multidisciplinary focus, personalised care and self-determination theory are included in the intervention described in this protocol. We believe that this may increase the likelihood of being able to show meaningful improvements in this diverse patient population.

The objective of this feasibility study is to determine if an early, personalised, programme of care involving holistic follow-up of people with minor stroke discharged from the hyperacute stroke unit (HASU) and rapid assessment clinic (RAC) is acceptable and can feasibly be delivered within the NHS.

It will address the following uncertainties:

Recruitment rate (percentage of eligible people agreeing to take part).Treatment adherence rate (percentage of people attending both follow-up appointments and engaging in agreed actions).Participant retention rate (percentage of those in the intervention and control groups that complete the final outcome measurement).Acceptability and accessibility of outcome measures.Ability to gather self-report data to complete an economic evaluation.Acceptability and perceived benefit of the follow-up intervention.

 If the feasibility objectives meet the predefined progression decision criteria and the intervention and outcome measures are accessible and acceptable to those with minor stroke, then the next stage will be to deliver a definitive multicenter trial to determine the efficacy of this complex intervention.

## Methods

### Patient and Public Involvement

A patient and public involvement group with experience of minor stroke was instrumental in the study conception and design. Three online group meetings with six attendees and the lead investigator took place to plan and design the study. A further two face-to-face meetings with people from underserved communities who did not wish to attend online group meetings were also held. Their input highlighted the challenges of online meetings, reading study documentation, and completing outcome measures on a mobile phone for those who do not have access to laptops or desktops. In the online and face-to-face meetings, the importance of the research idea was explored, the research question was agreed upon, the intervention was developed and refined, and this included participants’ input shaping the frequency and content of the follow-up appointments. An underpinning theory was presented, and its relevance and understandability were critiqued by the group. Outcome measures originally considered were excluded based on group feedback, and the final measures were agreed upon.

To improve the inclusivity of this research, perspectives and feedback from a diverse range of people were obtained. This included presenting the planned research to a group of ethnic minority women from an underserved community. Through this group, an improved understanding of the barriers and concerns of this community regarding follow-up care was developed, and recruitment processes were adapted accordingly. Our team was exposed to different health belief systems and attitudes towards disease and recovery. In addition, a group member reviewed the information sheet and the consent form. Based on her feedback, an accessible supplementary information sheet was developed, and improvements were made in the consent form.

Engagement with acute and community-based stroke clinicians in localities beyond our own confirmed that the lack of structured follow-up care for people after minor stroke also exists in other services. We learned about clinical services that are attempting to deliver different models of follow-up care to complement the narrow focus of stroke medical follow-up appointments. Addressing secondary prevention, adjustment to life after stroke, and assessment of ongoing therapy needs requires additional multidisciplinary staff in the clinic. Services described difficulties in obtaining substantive funding to enable stroke follow-up clinics to provide more holistic and personalised care. We are also engaged in an international collaboration with other researchers in this field. We are conducting a systematic review to collate the latest evidence on the lasting impairments experienced after minor stroke and TIA
^
29
^.

### Trial design

The current trial is a two-armed, parallel group, randomised, single-center, feasibility study with embedded qualitative interviews. Participants and the outcome assessor, a specialist occupational therapist (OT), will not be blinded to the intervention. The study flowchart is shown in the Consort Diagram
Figure 1.

**Figure 1. f1:**
[figure not shown]
Consort diagram.

This protocol has been reported in accordance with SPIRIT guidelines
^
30
^. The template for the intervention description and replication (TIDieR) checklist was used to report the intervention details
^
31
^. These documents can be found in the Open Science Framework Repository.
https://osf.io/gnw57/

### Setting

Recruitment: Participants with a NIHSS score of ≤5 at 2 hours post admission and meeting the other inclusion criteria will be recruited from the HASU and RAC. People attending the RAC are referred to the clinic via their GP or may have been seen in the emergency department and discharged home but with follow-up investigations to be completed in the clinic. Both the HASU and RAC are located in a high-density, ethnically diverse, urban environment.

Outcome measurement: Baseline measures for both groups will be conducted by the OT in the hospital where possible, but if the person is discharged quickly or seen in the RAC, then they will be conducted at the persons home or in the clinic. The final outcome measurement location will be agreed upon by the participant and could be in their home or in the hospital.

Intervention: Participants will determine their preferred location for follow-up appointments. They will be offered in-person appointments in the outpatient clinic at the hospital, appointments over the telephone or video call, or in their home or neutral venue in the community.

This personalised approach is based on PPI input into the study design and aims to increase the inclusivity of the study. Online appointments introduce digital exclusion and favour younger participants. On the other hand, having to travel to the hospital may be a deterrent for older participants or those who are back at work.

### Trial registration

ClinicalTrials.gov - NCT05897905 (22/05/2023)

Accessed at:
https://classic.clinicaltrials.gov/ct2/show/NCT05897905

### Protocol version

Protocol V4 (31/03/2023), approval date 21/07/2023.

Substantial amendment - SA01 – Protocol V5 (26.10.2023), approval date 06/02/2024.

### Eligibility criteria

**
*Inclusion criteria*
**

Adult ≥18Clinical or radiological diagnosis of minor stroke from a stroke consultant.Admitted to HASU or seen in RAC.Pre-admission modified Rankin Score (mRS) of 0–3 (see table below), with no formal package of care prior to stroke.
Table 1. Modified Rankin Scale scores
^
32
^
NIHSS ≤ 5 at 2 hours post admission.
Table 2. Stroke Severity – National Institute of Health Stroke Scale ScoreWithin one week of receiving stroke diagnosis.Discharge mRS of 0–3.No onward referral to community therapy team or for package of care.Has capacity to consent.

**Table 2. T2:** Stroke Severity – National Institute of Health Stroke Scale Score.

NIHSS Score	Stroke Severity
0	No Stroke symptoms
0–4	Minor Stroke
5–15	Moderate Stroke
16–20	Moderate to Severe Stroke
21–42	Severe stroke

**
*Family member inclusion criteria for qualitative interview (SA-01)*
**

Family members or partners who participated in and/or supported the researcher with the recruitment process, intervention delivery, and outcome measurement.

**
*Exclusion criteria*
**

Any serious comorbidities that would impact a person's ability to participate in follow-up appointments and outcome measurement.Insufficient English to engage in intervention and outcome measures, and no family or friends to support with this.Not resident in England.Pregnant women.Enrolled in another interventional trial that does not allow co-enrolment or observational studies where the burden of assessment may be too high.

### Participant identification, screening and recruitment

The researcher will review the electronic records of all new admissions to the HASU. If the patient meets the study criteria, eligibility is confirmed by the assessing team. This process is followed for weekend admissions. If the researcher is unable to attend the ward in person prior to discharge, then consent for contacting the patient post-discharge will be obtained and documented. In the RAC, potential study participants will be identified by stroke clinical nurse specialists, and consent will be obtained for the researcher to contact the person following discharge. Consent for participation in the study will be completed by the researcher either on the ward or in the clinic or at the participant’s home.

Data will be collected to capture the baseline and clinical characteristics of those approached for study involvement as well as their ethnicity, and level of education (
Table 3).

**Table 3. T3:** Participant data collection domains.

Pre-Stroke Information	Admission Information	Discharge Information
mRS Past medical history Clinical Frailty Scale (CFS) Employment status PHQ2 EDI information: - Ethnicity - Age - Education level	NIHSS* Hyperacute treatments • Thrombolysis • Thrombectomy • Both • Neither	NIHSS mRS MoCA Length of hospital stay

Table 3 key: mRS-modified Rankin Scale, PHQ2-patient health questionnaire 2, EDI-ethnicity, diversity and inclusion, NIHSS-National Institute of Health Stroke Scale, MoCA-Montreal cognitive assessment.

Strategies to promote recruitment: Therapy staff within the stroke service are rotational; therefore, regular study updates will be given to the therapy team by attending their fortnightly team meetings. A template of what to write in the patient record when approaching a potential study participant will be provided, and the study inclusion and exclusion criteria will be clearly displayed on the therapy information board on the ward.

The recruitment target is five participants per month from the HASU. This target is based on pilot data; people with minor stroke were recruited from the HASU over a three-month period to a two-week follow-up study involving online cognitive testing
^
33
^. No preliminary data gathering was conducted at the RAC, but time was spent in the clinic to understand what a clinic appointment involves for the patient. A smaller proportion of people who attend this clinic will receive a diagnosis of stroke; therefore, the recruitment target is set at two participants per month.

### Randomisation

Participants will be randomised to the intervention or control group by simple randomisation using a 1:1 allocation ratio and opaque sealed envelopes to ensure allocation concealment. Randomisation will be stratified by recruitment location to ensure treatment assignment is balanced between the two groups within each location.

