### Sample size

Progression criteria related to feasibility outcomes were identified. We plan to recruit 60 participants (30 in the control group and 30 in the intervention group) in line with sample sizes for similar feasibility studies
^
34
^. Feasibility studies need to be much smaller than full-efficacy trials to be considered worthwhile. The feasibility outcome “participant retention” is the percentage of 60 participants who complete outcome measurements at 12 weeks. Using a binomial probability confidence interval (CI) calculator with a sample size of 60, the 95% CI on proportions will have widths no greater than 37% (based on the 50% proportion having a 95% CI from 37% to 63%. Proportions further from 50% would have narrower CIs; for example, 90% has a 95% CI from 79–96%, so this CI has a width of 17%.
Free Binomial Probability Confidence Interval Calculator - Free Statistics Calculators (danielsoper.com)

The width of these CIs provides a reasonable balance between the cost and practicality of patient recruitment. The feasibility outcome “recruitment uptake” would have narrower CIs (since 60 is the numerator with a larger denominator). There is no relevant power calculation because the main outcomes are proportions rather than anything that can be assessed using hypothesis testing.

The progression criteria targets are described in
Table 4. They provide a guide through the use of a predefined traffic light system of red (stop), amber (amend, modifications needed), and green (proceed), as to whether the study could proceed to a future definitive trial. The targets may seem ambitious, but due to the limited number of appointments and personalised nature of the intervention, where participants do not need to attend appointments at the hospital, we believe these are achievable. We have carried out extensive work with diverse community groups that has improved our understanding of culturally appropriate ways to approach patients from different communities. Further, this is also a single-centre study, with the lead researcher having established working relationships with the other members of the stroke team.

**Table 4. T4:** Progression decision criteria.

FEASIBILITY OBJECTIVES	MEASURES USED	DENOMINATOR FOR PERCENTAGE	GREEN Proceed to full scale trial	AMBER Amendments needed	RED Definitive trial unlikely to be feasible
1. Recruitment uptake	% of eligible people agreeing to take part	Over 60 (numerator is 60)	≥90%	60–89%	<60%

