2. Treatment adherence	% of participants that attend both follow-up appointments	30 (patients recruited into treatment arm)	≥90%	60–89%	<60%
3. Participant retention	% of participants that complete outcome measures at 12 weeks	60 (all recruited patients)	≥90%	60–89%	<60%

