**Other variables being measured**						
mRS routinely collected	x				x	
Cognition screen	x				x	
Training material feedback				x		
Mood measures						
PHQ2	x					
PHQ9					x	
GAD7					x	
Economic info						
Health and social care usage		x		x	x	
Work status	x				x	
Admin, programme delivery time	x	x	x	x	x	x
Qualitative interview						x

Table 5 key: HCCQ-Healthcare Climate Questionnaire, PROMIS-10-Patient-reported outcome measurement information system, PEI-Patient enablement instrument, SA01- Substantial amendment 1, mRS-modified Rankin scale, PHQ2-Patient health questionnaire 2, PHQ9-Patient health questionnaire 9, GAD7-Generalised anxiety disorder

1. Recruitment rate (Time point 0 = T0): Proportion of participants randomised relative to the total number meeting the inclusion criteria. Reasons for declining participation will be recorded. The ability to gather baseline and EDI data will be noted as will acceptability of randomisation.

2. Treatment adherence rate (Time point 3 = T3): Proportion of participants in the intervention group who attend both follow-up appointments. When people drop out reasons for this will be obtained.

3. Participant retention rate (T4) - Proportion of all participants that complete the follow-up questionnaires.

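### Simple 1:1 randomisation, even on separate lists for each recruitment location, does not ensure the within-location balance that the protocol claims for it

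*Protocol article*

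**What the plan says.** The Randomisation section has two sentences. The first says participants are "randomised to the intervention or control group by simple randomisation using a 1:1 allocation ratio", with "opaque sealed envelopes to ensure allocation concealment". The second says: "Randomisation will be stratified by recruitment location to ensure treatment assignment is balanced between the two groups within each location". The envelopes are offered as a means of concealment only. No block size, minimisation, or fixed number of envelopes per arm or per location is mentioned anywhere in the article.

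Four other places bear on the point:

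- Sample size gives the planned arms as "30 in the control group and 30 in the intervention group".
- Table 4 gives the denominator of the adherence criterion as "30 (patients recruited into treatment arm", followed by a closing bracket.
- Primary feasibility outcomes defines adherence without a fixed number: "Proportion of participants in the intervention group who attend both follow-up appointments".
- Statistical methods plans confidence intervals for changes within each group and for between-group comparisons of those changes, to help choose the primary outcome of a definitive trial.

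**The concern.** A stratified scheme balances the arms within a stratum only if the sequence in each stratum is restricted, for example by permuted blocks. Under simple randomisation each participant is an independent fair draw, so two lists behave exactly like one and balance is left to chance. The second sentence therefore claims a property that the method in the first does not have. A fuller protocol could add detail, but no added detail would make both sentences true as written.

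Two things are at stake. First, readers cannot tell how the sequence was made. They need to know that to judge how predictable it was, especially as the lead researcher takes consent, delivers the intervention and takes the measurements, unblinded. Second, the investigators chose location as the factor to balance, presumably because the two routes differ: RAC patients come through their GP or after emergency department discharge, HASU patients by admission. The stated method does not protect that balance, and the RAC stratum is small.

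**Working it through.** **Inputs.** Total 60, with 30 per arm planned (Sample size). Allocation probability 0.5 per participant (Randomisation). Monthly recruitment targets of five from the HASU and two from the RAC (Participant identification, screening and recruitment).

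**The plan's own figure.** Expected arm size = 60 × 0.5 = 30. The stated 30 per arm is reproduced, as an expectation.

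**Why separate lists change nothing.** If n₁ participants come from the HASU and n₂ from the RAC, the intervention arm is Binomial(n₁, 0.5) + Binomial(n₂, 0.5) = Binomial(60, 0.5), whatever n₁ and n₂ are. Within each location the arm size is likewise an unrestricted binomial.

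**Overall arm size, X ~ Binomial(60, 0.5).**

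- Standard deviation = √(60 × 0.5 × 0.5) = 3.87.
- The 2.5% and 97.5% quantiles are 22 and 38. The range 22–38 has probability 97.3%, and 23–37 has 94.8%.
- Arms differing by 10 or more means 35:25 or worse: 2 × P(X ≥ 35) = 24.5%.
- P(X = 30) = C(60, 30) / 2⁶⁰ = 10.3%.

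**Within the RAC.** If both monthly targets are met in proportion, the RAC supplies 60 × 2/7 = 17.1, taken as 17, and the HASU 43. The article does not fix these stratum sizes, so they are an assumption.

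- 12:5 or worse among 17: 2 × (6188 + 2380 + 680 + 136 + 17 + 1) / 2¹⁷ = 18804 / 131072 = 14.3%.
- Range for a similarly uneven split: with 10 RAC participants, 7:3 or worse has probability 2 × (120 + 45 + 10 + 1) / 1024 = 34.4%. With 20, 14:6 or worse has probability 2 × 60460 / 1048576 = 11.5%.
- With strata of 43 and 17, the arms come within one participant of each other in 23.9% of cases in the HASU and 37.1% in the RAC. Both happen together in 0.239 × 0.371 = 8.9%.

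**What a restriction would deliver.** Permuted blocks within location bound the imbalance. The ranges follow from the block size. The last column is from 40,000 simulated runs, with the HASU count drawn as Binomial(60, 5/7).

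| Block size | Largest arm difference within a location | Range of the intervention arm | Exactly 30/30 |
|---|---|---|---|
| 2 | 1 | 29–31 | 75% |
| 4 | 2 | 28–32 | 62% |
| 6 | 3 | 27–33 | 54% |

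Blocking delivers near-balance in each location. It still does not guarantee exactly 30 per arm, because the last block in each location may be incomplete.

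**The case against.** The best defence is that *simple* is loose wording for a restricted set of envelopes, and that the detail sits in the full protocol, which the article says is deposited. That may be so, and the absence of a block size from a journal article is no fault in itself. But the article does not say the set was restricted, and the word it uses means the opposite. Even shuffled envelopes with fixed counts per arm would balance a location only if all of its envelopes were used.

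Three stronger readings are tempting, and the documents do not support them.

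- **That the adherence criterion will be miscalculated.** With a literal denominator of 30, an arm of 26 or fewer (probability 18.3%) could never reach green, since 26/30 = 86.7%. An arm of 34 would reach green with 27 attenders, whose true adherence is 27/34 = 79.4%. But Table 4 glosses its 30 as the patients in the treatment arm, and Primary feasibility outcomes defines adherence over the intervention group with no number attached. The natural reading is a planned figure with its definition beside it.
- **That 30 per arm is treated as certain.** Sample size presents it as a plan, and blocking would not guarantee it either. Simple randomisation puts the arm within 27–33 in 63% of cases (1 − 0.366). The cost in precision is modest even in the tail. An arm of 22 or fewer has probability 2.6%. At 22 the widest Clopper-Pearson interval is 43.6 points (11/22: 28.2–71.8%), against 37.4 at 30 (15/30: 31.3–68.7%).
- **That the between-group comparisons are confounded by care route.** Chance imbalance under valid randomisation is not systematic bias. The comparisons serve to review responsiveness, the article disclaims hypothesis testing for its main outcomes, and no efficacy conclusion rests on them.

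**Conclusion.** The contradiction stands. The stated method does not have the property claimed for it, and one of the two sentences must change. The overall figures (22 to 38 in the intervention arm, and a 24.5% chance that the arms differ by 10 or more) rest only on 60 independent fair draws. The 14% for the RAC also rests on the assumed 17 participants there.

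This is a moderate correction, not one on which the trial's conclusions turn. The recruitment and overall retention criteria do not involve the arm split, and the adherence percentage is right provided the number actually randomised to intervention is used. What remains is an inaccurate account of the allocation method and a small stratum whose balance is unprotected if that account is literally true.

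**What to change.** 1. State in the Randomisation section how the envelopes were actually generated. If the sequence was restricted (for example permuted blocks within location), delete *simple* and name the method. If it was unrestricted, delete the claim that balance is ensured and present 30 per arm as the expected size.
2. Include recruitment location as a factor in the between-group comparisons of change already planned in Statistical methods. This suits either case: it respects the stratification if the sequence was restricted, and allows for chance imbalance if it was not.
3. As a minor clarification, word the Table 4 adherence denominator as all participants randomised to the intervention arm (planned 30), in line with Primary feasibility outcomes.
4. Specify restricted randomisation within strata for the definitive trial, so that the contradiction is not carried forward.

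Trial status reports recruitment closed, so nothing about the allocation itself can or need change. The cost is a few words in two places and one factor in the analysis.
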